## Methods

In close partnership with the SDP this study encompasses a rigorous implementation mapping procedure to improve the implementation and public health impact of USM within SDP schools [38, 50]. This pilot project began with identifying key determinants of implementation and desired outcomes through a rigorous needs assessment which accomplished Task 1 of implementation mapping [47]. This task was completed intentionally before the trial to allow time for the research team to 1) build partnerships with schools in the district and show investment (which took considerable time) and 2) conduct a needs assessment with a larger sample of schools prior to setting up a cluster-randomized trial.

### Theoretical framework and preliminary findings

Figure 1 depicts the conceptual framework for our implementation mapping process, which is described in full below.

**Fig. 1 Fig1:**
[figure not shown]
Conceptual overview of the implementation mapping project

Task 1 identified key determinants of USM implementation for addressing health disparities across 8 schools (6 elementary/middle; 2 high) within SDP. This task was completed over the 2023–2025 school years, grounded in the CFIR (v2) [51] and Health Equity Measurement Framework (HEMF) [52] and was recently published [47]. Among 8 schools, 193 participants completed surveys and/or interviews grounded in the CFIR including students in middle (14%) and high school (10%) grades, parents (26%), food service staff/managers (11%), teachers (25%), and administrators (14%). Findings revealed significant concerns with food insecurity expressed by participants at each level of the school system, and viewpoints among parents and staff that USM is essential for ensuring students are ready for learning. Key barriers were perceptions among students and parents that their views are not prioritized in USM implementation, which could limit desires to participate in school meals. Participants in all groups discussed challenges in uptake due to students bringing food in from competitive vendors (i.e., corner stores & fast food restaurants) and a lack of affordable grocery stores in the school vicinity, limiting students’ socialization to healthier foods such as those provided in the school menu [47]. These findings heavily inform our protocol design and methods.

The GTE [7] and the Exploration, Preparation, Implementation, Sustainment (EPIS) [53] frameworks will ground Aim 1 (Tasks 2–4) to guide the selection and tailoring of implementation strategies and protocols [7, 54]. The GTE was developed to inform operationalization of equity principles and concepts in PSE approaches related to obesity, in partnership with members of the community of interest. GTE guidance prompts for identifying and addressing intervention design features and contextual variables to improve equity impact, accounting for individual and community-level resources and capacity [7]. The EPIS framework [53] conceptualizes key phases of Exploration (deliberating ways to innovate/the innovation), Preparation (planning for implementation), Implementation (the process of implementing), and Sustainment (maintaining implementation) that guide and describe the implementation process. Similar to CFIR, EPIS provides a set of constructs among key domains of outer context (outside the school system) and inner (within school) context across these phases, bridging factors that span across inner and outset settings, innovation factors, and role of innovation adopters. Together, these frameworks will support the co-development process, ensuring that strategies and protocols developed are grounded in addressing inequities in access (GTE), and that we have a strong structure (EPIS) that facilitates consideration of key determinants and processes over discrete phases of the mapping process.

Primary implementation outcomes aligning with Proctor et al.’s framework [55] will be collected in Aim 2 (Task 5) to evaluate the resultant implementation strategy through a Hybrid Type III Design [56]. Chosen outcomes are penetration (i.e., degree to which school meals were provided equitably to low-income students) and cost (i.e., time, labor, supplies needed). Additional implementation outcomes include acceptability (i.e., degree of satisfaction); feasibility (i.e., practicality of strategy); and sustainability (i.e., maintenance of intervention) [57]. Secondary student-level outcomes will be assessed to understand behavioral impact of the implementation strategy on student weight status, family food security, and dietary behaviors. The EPIS framework will also support evaluation of key implementation determinants and processes over the evaluation period to triangulate implementation and behavioral outcome data.

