**Fig. 2 Fig2:**
[figure not shown]
Flow chart of hybrid trial

We will systematically map barriers and strengths identified in Task 1 to USM implementation provided by diverse school and district representatives (i.e., food service providers, teachers, administrators, students, and parents) on to potential strategies based on prior work [58]. The goal of establishing performance objectives (Task 2) will be determined by our findings from Task 1 and by the key goal of increasing student participation in USM. For Task 3, strategies can be from one of many categories including planning (e.g., building stakeholder buy-in); education (e.g., training implementers); financial (e.g., incentives); structural (e.g., create teams); management (e.g., audit and feedback); or policy-related (e.g., licensure standards) [37]. Instead of the initial compilation of strategies developed for clinical settings, which use clinical terms (i.e., patients, providers), [37] our team will primarily consult strategy compilations tailored to the education [58] and community settings [59]. This process ensures we are following the most recent literature and guidance based on pragmatic trials. Grounded in GTE constructs, one potential implementation strategy from the “planning” category could be to assemble a group of students for an advocacy group, who would take a leading role in promoting school meal participation and collaborate with school food service. For Task 4, materials and protocols will be developed grounded with specific attention to the four GTE constructs [7]. These materials will outline what messages, methods, and materials are needed to carry out the chosen strategy through an equity lens. For example, if “planning” is the implementation strategy, specific communication practices may be created to recruit students and engage them in leadership activities based on needs in Task 1 [7].

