### Aim 2: evaluate implementation and student-level outcomes of the strategy using a hybrid type III implementation-effectiveness design

Following the hybrid type III approach, [56] a longitudinal convergent (Quantitative–Qualitative) mixed-methods design will investigate the impact of this trial. Primary implementation outcomes of penetration/reach will be calculated through analyzing participation rates from breakfast and lunch service across the implementation period. We will create an implementation costing measure to calculate the financial cost of each implementation strategy. Additional outcomes of acceptability (i.e., are representatives satisfied with this strategy?), feasibility (i.e., was this simple to carry out?), and sustainability (i.e., could this be maintained?) will be assessed from the perspective of implementers. Implementation objectives identified in Task 2 will be evaluated through brief, semi-structured interviews with implementing representatives*.* Secondary student health outcomes of weight status, food insecurity, and dietary behaviors will be analyzed over the 2-year implementation period.

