#### Participants and procedures

Intervention school teams will receive coaching during the implementation phase with monthly check-in meetings at school sites or via phone/Zoom if necessary (~ 15–30 min) to support implementation efforts and retention of schools across the intervention period. Implementation leaders and other front-line implementers (i.e., food service staff) from intervention schools will be asked to complete surveys and brief interviews to address implementation outcomes. Administrators and food service providers will be asked to participate in interviews which will facilitate the development of the costing measure. Penetration and behavioral data for all 4 schools will be collected before Aim 1 begins and throughout study completion. Table 1 illustrates the implementation (in green) and behavior/health outcome (in blue) measures we will collect, the source, data collection period, and the timing/frequency of these measures for the hybrid type III implementation-effectiveness study.

**Table 1 Tab1:** Hybrid type III study: overview of variables, data source, collection period, and timing/frequency of data collection

	**Variable**	**Source**	**Data Collection Period**	**# Time Points/Frequency**
**Implementation Outcomes**	Penetration (Meal Participation)	Division of Food Services	Daily for Breakfast and Lunch	Monthly Average (%) per student
	Cost	Cost Survey and Interview	Fall and spring each year	4 (2 in each trial year)
	Acceptability	Implementation Survey	Fall and spring in first year	2
	Feasibility	Implementation Survey	Fall and spring in first year	2
	Sustainability	Implementation Survey	Fall and spring each year	4 (2 in each trial year)
	Implementation Determinants	Check-in Meetings	Monthly	18 (9 each year)
**Behavior/Health Outcomes**	Race, ethnicity, economic disadvantage	District database	Fall of each year	2
	Weight Status/BMI	Office of Health Services	Fall of each year	2
	Student hunger, self-reported participation, dietary behavior	Office of Research and Evaluation	Spring of each year (student survey)	2
	Attendance	District Database	Daily for each student	Monthly Average (%) per student

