#### Data collection and primary outcomes

The number of breakfast and lunch meals served (linked to student ID) will provide data on penetration, facilitating assessment of equitable access to low-income students. For cost of implementation, Our team will develop a bottom-up costing strategy and measure the costs for each implementation strategy that results from the mapping process, following guidance from experts in economic evaluation of implementation [49, 66] and in collaboration with our CAB and school district partners. We will do this by establishing categories of resource use for each strategy (e.g., labor, materials, travel) and developing initial measures to capture time and effort of all implementing participants at the school sites. We will then conduct a budget impact analysis and costconsequence analysis to enhance understanding of the value for each strategy and determine potential for scale-up. Validated surveys adapted for the school context by the principal investigator (see additional file 3) will provide data on acceptability, feasibility, and sustainability of the implementation strategy by each member of the implementation team [67–69]. Finally, brief (i.e., 20–30 min) interviews will be held with key implementing representatives (identified in Task 1) to identify the degree to which implementation objectives were met grounded in the GTE toward the end of the first year of implementation [38, 44, 45]. We will also ask about overarching facilitators and barriers during these interviews, mapping determinants to the Implementation and Sustainment phases of EPIS. To support replicability of our protocol, all surveys, interview guides, coding materials, and other pertinent documents will be made publicly available on our lab website and through article publication.

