#### Analyses

Overall, the longitudinal data collection at baseline, 6 months, and 12 months following the inception of the trial will facilitate assessment of change over time and identification of factors that influence the outcomes. For the implementation outcomes, penetration will be analyzed by calculating the proportional change in number of low-income students participating in USM from prior to enacting the implementation strategy at baseline, 6 months, and 12 months following the start of the trial. For the costing measure, labor costs will be iteratively analyzed through the bottom-up approach to collect time and effort data from all implementing individuals; salary data will be obtained for all SDP positions through review of publicly available records. Receipts and invoices for all materials and miscellaneous costs will be analyzed. All costs will be calculated specific to each strategy to allow for accurate reporting and budget impact assessment showing net financial costs resulting from the strategies. The costconsequence analysis will be conducted to show the comparison of the costs and outcomes of each strategy in comparison to the waitlist condition (i.e., treatment as usual) [49, 72]. Data from the acceptability, feasibility, and sustainability surveys will be processed and aggregated at the school level to provide overall means. Interview data on other outcomes identified through the mapping procedure will be analyzed deductively through the GTE and Proctor outcomes framework [7, 57] followed by mapping ongoing determinants to the EPIS framework in the Implementation and Sustainment phases, providing tangible barriers and facilitators across the trial period [53]. This will enhance continuation of determinants analysis from Aim 1 and support adaptation/tailoring of the implementation strategies over time in response to needs/challenges at each school. Such adaptation is recommended by implementation science experts as a means to enhance equity through collaborations with community and clinical partners [43].

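### Penetration is defined as equity of provision to low-income students, but no stated analysis compares them with other students, so the change in the gap is left unmeasured

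*Protocol article*

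**What the plan says.** Three places in the protocol article describe penetration.

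- **Theoretical framework and preliminary findings** defines it as "penetration (i.e., degree to which school meals were provided equitably to low-income students". Data collection and primary outcomes, under Aim 2, gives the meal records the same purpose: "facilitating assessment of equitable access to low-income students".
- **Aim 2, Analyses**, gives the calculation: "penetration will be analyzed by calculating the proportional change in number of low-income students participating in USM", from before the strategy starts and at baseline, 6 months and 12 months.
- **Aim 2, opening paragraph**, describes it differently: "Primary implementation outcomes of penetration/reach will be calculated through analyzing participation rates from breakfast and lunch service across the implementation period". Income is not mentioned there.

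On the data, Table 1 lists meal participation as "Monthly Average (%) per student", and Participants and procedures adds: "Penetration and behavioral data for all 4 schools will be collected before Aim 1 begins and throughout study completion". Data sources and secondary outcomes says that students enter their ID at the point of sale whenever they take a meal. It also says that the district holds a binary economic-disadvantage variable, and that this is among the datasets to be merged with the meal records.

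**The concern.** Whether something is provided equitably is most naturally a comparison: how low-income students fare relative to others offered the same free meals in the same schools. One stated calculation looks at low-income students alone, and the other pools everyone. A result on either could be good or poor for equity, depending on what the other income group did. The article's Discussion and Summary speak of equity-driven strategies and of more equitable access. If those statements are meant to describe a disparity that changed, the primary quantitative outcome as written would not support them.

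A second weakness is that the Analyses sentence uses a change in a number of students. A number moves with enrolment as well as with participation.

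**Working it through.** The article gives no target, power or income-specific participation rate for penetration, so there is no planned figure to reproduce. The check asks whether the stated measures determine the gap.

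**Assumed inputs (not in the documents).** 300 low-income and 100 other students. Before: 50% of low-income and 60% of other students participate. After: 55% of low-income students participate, and the rate in other students varies.

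**Formulas.**
- Stated measure = (low-income participants after ÷ low-income participants before) − 1.
- Gap = other students' rate − low-income rate. At baseline: 60 − 50 = 10 points.

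**1. Count of low-income participants.** Before: 300 × 0.50 = 150. After: 300 × 0.55 = 165. Stated measure: 165 ÷ 150 − 1 = +10% in each of these rows.

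| Other students after | Stated measure | Gap after | Gap change |
|---|---|---|---|
| 60% | +10% | 60 − 55 = 5 points | narrows by 5 |
| 65% | +10% | 65 − 55 = 10 points | none |
| 72% | +10% | 72 − 55 = 17 points | widens by 7 |

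**2. Count against rate.** Let low-income enrolment grow from 300 to 330 with participation still at 50%: 330 × 0.50 = 165, and 165 ÷ 150 − 1 = +10%. Neither the low-income rate nor the gap has changed.

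**3. Overall rate, as in the opening of Aim 2.** Before: (150 + 60) ÷ 400 = 52.5%. If low-income students reach 55% and others stay at 60%, the overall rate is (165 + 60) ÷ 400 = 56.25%, with a gap of 5 points. If low-income students stay at 50% and 75 of the 100 others participate, it is (150 + 75) ÷ 400 = 56.25%, with a gap of 25 points. The pooled rate does not fix the gap either.

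**4. The gap alone.** If other students fall from 60% to 50% and low-income students stay at 50%, the gap goes from 10 points to 0 although no low-income student gained a meal. The gap therefore needs the low-income change beside it.

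**5. Do the regression models fill the hole?** The hierarchical models under Aim 2, Analyses, are described for the behavioral outcomes. Table 1 places penetration among the implementation outcomes, so the article does not apply those models to it.

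**The case against.** The strongest reply is that equity here means reach in the disadvantaged group. The Background describes programs that fail to reach their target population and asks for more reach among low-income youth. The definition names low-income students as the recipients, and no section reports an income gap in participation or makes narrowing one an aim. On that reading the low-income calculation fits the definition, and the equity language describes how the strategies are developed. This reading is possible, but it leaves the word *equitably* without any measure, and the definition, the opening of Aim 2 and the Analyses sentence still describe different things.

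It can also be said that an article condenses, and that a contrast by a covariate already merged could sit in an analysis plan that is not shown. That would answer silence. Here the article states a definition and then a specific calculation that does not measure it.

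Several stronger readings are tempting, and the documents do not support them:

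- *The trial cannot tell whether the gap changed.* It can. Meals are recorded per student in all four schools and merged with the income flag.
- *Other students never enter the analysis.* That is true of the Analyses sentence only; the participation rates in the opening of Aim 2 are not restricted by income.
- *The goal of higher overall participation goes unanswered.* The phrase "by the key goal of increasing student participation in USM" concerns how Task 2 performance objectives are set, not the definition of the primary outcome, and the opening of Aim 2 covers overall participation.
- *A closing gap would be missed.* A gap that closes because low-income participation rises does register on the planned measure; what goes unseen is its effect relative to other students.
- *A widening gap would be declared an equity success.* The article states no such decision rule.

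**Conclusion.** The point holds as an inconsistency between a primary outcome's definition and its stated analyses. Neither stated analysis contrasts income groups. In the illustration, the same +10% is compatible with a gap of 5, 10 or 17 points after a baseline of 10, and a count can produce +10% from enrolment alone. These sizes rest on assumed rates and numbers; the argument needs only that participation in other students is free to move. It also rests on reading *equitably* as comparative. If the authors mean reach among low-income students, the remedy is to say so and limit the conclusions to that. The matter is worth settling before analysis because it decides what a primary outcome measures, but it is no flaw in the design or in data collection.

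**What to change.** 1. Reconcile the definition in Theoretical framework and preliminary findings with the opening of Aim 2 and with Aim 2, Analyses, so that penetration is one quantity throughout.
2. Analyse participation rates, not counts, in all students, with the economic-disadvantage flag as a factor.
3. Report by arm the change in participation overall, in low-income students, in other students, and in the gap between the two groups.
4. Base any statement about a disparity on the gap read together with the change in low-income students, so that a gap closed by falling participation in others is not counted as success. Otherwise limit the conclusion to reach among low-income students.

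The cost is a few lines of analysis wording and no new data. The limitation is precision. There are two schools per arm, and the share of flagged students in them is not given; the Background says only that eligibility for universal meals starts above 25% low-income students. If nearly all students are flagged, the comparison group will be small. The gap estimate should be presented as descriptive, with its imprecision shown.

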### Community advisory board

To meaningfully guide this work and ensure our methods are grounded in community member voices, over the last 2 years we have recruited and retained a Community Advisory Board (CAB) comprising individuals (*N* = 10) from academia (*n* = 2), non-profit organizations (*n* = 2), the Philadelphia Department of Public Health (*n* = 1), food service representatives (*n* = 1), former teachers (*n* = 1), parents (*n* = 1), and students in high schools (*n* = 2). This CAB was developed in 2023 at the start of the needs assessment phase (Task 1) and has served as an invaluable sounding board for the 5-year study; for Task 1 (needs assessment) all CAB members reviewed interview guides, analysis protocols, and co-designed dissemination products for our work. All CAB members receive financial compensation for their involvement as acknowledgement of their expertise and effort. Now in its second year, the CAB serves a more embedded role within our research and has supported recruitment of schools, fundraising, partnerships with other organizations in the city, and dissemination efforts beyond peer-reviewed literature. The CAB will continue to support our work and play a greater role related to Task 2–5; examples are outlined in the methods and discussion sections.

### Aim 1: use a community-engaged procedure to develop an equity-focused implementation strategy through a cluster randomized design

Informed by findings from the needs assessment (Task 1) [47], this aim will comprise identifying goals for implementation and objectives (Task 2), the development and tailoring of implementation strategies (Task 3), and implementation protocols (Task 4) for USM implementation through a cluster-randomized pilot design. From the schools in the needs assessment sample, two will be block randomized to receive implementation strategy selection support and two will implement USM as usual as a waitlist comparison group, before going through strategy development the following year (Fig. 2). Schools will not be blinded to this randomization given that they will be asked to sign a collaboration agreement and will be told whether they are completing mapping first or assigned to the waitlist condition. Eligible schools are those that have participated in our needs assessment or have agreed to collaboration through a formal agreement and are a public, non-charter school within the SDP.

